### Ascertainment of outcomes

Outcomes measured at the level of families and children’s centres will be ascertained using a range of tools delivered as summarised in Table 1 and described below.

**Table 1 T1:** Tools for measuring parent and children’s centre outcomes by treatment arm

**Data collection tool**	**IPB plus facilitation arm**	**IPB only arm**	**Control arm**
*Data collected from families*			
Baseline self-completion questionnaire	x	x	x
Post-intervention self-completion questionnaire	x	x	x
*Data collected from children’s centres*			
Baseline manager/staff questionnaire	x	x	x
Post-intervention manager/staff questionnaire	x	x	x
Facilitation contacts questionnaire at 1, 3, 4/5 and 8 months	x	x	
Facilitation contacts interview at 1, 3, 4/5 and 8 months	x	x	
Activity logs	x	x	x
Post-intervention facilitation questionnaire	x	x	
Post-intervention facilitation interview	x	x	
Post-intervention implementation fidelity questionnaire	x	x	
Post-intervention implementation fidelity interview	x	x	

*Note*: post intervention is 12 months post commencement of the intervention in the IPB plus facilitation and IPB only arms and at 12 months post randomisation in the control arm.

### Ascertaining family outcomes

The baseline self-completion questionnaire will include questions on socio-demographic and economic characteristics, information about the household, previous fire-related injuries, fire safety behaviours and fire safety equipment, knowledge and understanding of what causes fires, home safety information provided by children’s centres and satisfaction with this information. Questions on fire safety behaviours and fire safety equipment will be based on those used in structured interviews of parents attending children’s centres in the four trial sites previously undertaken to inform the trial [24]. This questionnaire will be piloted on families attending children’s centres not taking part in the trial.

The post-intervention questionnaire will adapt the baseline questionnaire to include questions about resource use and expenditure incurred as a result of the intervention or relevant sessions offered by the control centres; i.e., travel costs to attend educational sessions, equipment purchased and services attended (e.g. smoking cessation). Shorter versions of the questionnaire will be used for reminders; up to two reminders will be used. A range of methods will be used for questionnaire administration including postal, face-to-face completion with children’s centre staff or researchers or telephone completion. Families completing questionnaires will be provided with a £5 gift voucher for use in local stores as small monetary incentives have been shown to increase response rates in a previous systematic review [26,27].

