### Allocation to intervention and delivery of intervention

Once the required number of families have been recruited at a children’s centre, the children’s centre will be randomised to one of three arms: IPB plus facilitation, IPB only or usual care (control arm) (see below for method of randomisation). The intervention will be delivered over 12 months.

Children’s centres in the IPB plus facilitation arm will be given the following:

a) The fire prevention IPB containing (i), information for children’s centre managers on why preventing fire-related injuries is important, who the target group is, what interventions can be provided, creative ways of reaching the target group and how to evaluate their use of the IPB and (ii), information for children’s centre staff on why preventing fire-related injuries is important, who is at greatest risk, what are the main causes of house fires, what staff can do to help, what works to prevent house fires, where to get specialist advice and help and examples of activities they can do with parents, including session plans and resources covering smoke alarms, fire escape plans, the causes of house fires, children’s development and behaviour and risk of house fires and bedtime safety routines. Children’s centres will be asked to deliver the fire prevention messages to families participating in the trial over a twelve month period, using whatever format they think is most appropriate for their families. If they are unable to deliver all messages, they are asked to focus on smoke alarms and fire escape plans as these are the most evidence based.

b) A training session will be provided by the Child Accident Prevention Trust and the research team focussed on the IPB and its potential use within a children’s centre setting. This comprises an introduction to children’s injuries in general and fire-related injuries in particular; the development, principles and content of the IPB, opportunities to practice using the IPB and to develop an outline plan for how the IPB might be implemented and a discussion of data collection requirements for the trial.

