### Outcome measures

#### Definition of primary and secondary outcome measures

The primary outcome will be the proportion of families who report that they have a fire escape plan at 12 months follow-up.

Secondary outcome measures will include:

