### Blinding

It is not possible to blind children’s centre managers and staff or those providing the intervention to treatment arm allocation. As with many public health interventions, it is not possible to blind families to receipt of the intervention and as outcomes are self-reported, data on these cannot be collected blind to treatment arm allocation. If parents require support from a researcher to complete the follow-up questionnaire the researcher will not be blind to children’s centre treatment arm. Analyses will be undertaken blind to treatment arm allocation.

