### Qualitative analysis

Data from the telephone and face-to-face facilitation contacts between children’s centres and researchers will be analysed manually using content analysis after categorisation into main sub-headings [31]. A thematic analysis will then be conducted. Data from the 12 month implementation fidelity interviews will be managed using a qualitative data management package e.g. QSR NVIVO and analysed using Framework Analysis [32]. This is a structured method of qualitative data analysis where a priori themes are identified but emergent themes can also be identified and incorporated into the analytic framework. These themes will be agreed by researchers from the four trial sites and lay research advisors through an initial analysis of eight interviews, selected to represent a range of children’s centres. This framework will be used to undertake the analysis of the rest of the interviews, with further adaptation if required.

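### Children's centre staff may complete the follow-up questionnaire with families, although in the two IPB arms their centres are asked to deliver the message that the self-reported primary outcome measures

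*Protocol article*

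**What the plan says.** The article (Definition of primary and secondary outcome measures) sets the primary endpoint as a self-report: "The primary outcome will be the proportion of families who report that they have a fire escape plan at 12 months follow-up".

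The paragraph on the post-intervention questionnaire (Ascertaining family outcomes) lists postal administration and "face-to-face completion with children’s centre staff or researchers or telephone completion". Table 1 labels the tool a self-completion questionnaire in all three arms.

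On delivery (Allocation to intervention and delivery of intervention): "Children’s centres will be asked to deliver the fire prevention messages to families participating in the trial over a twelve month period". Centres that cannot cover every message are asked to concentrate on smoke alarms and fire escape plans.

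On masking (Blinding): "It is not possible to blind children’s centre managers and staff or those providing the intervention to treatment arm allocation". The section adds that families cannot be blinded, that self-reported data therefore cannot be collected blind, and that if a parent needs a researcher's support at follow-up, "the researcher will not be blind to" the centre's arm. It does not say that centre staff may also act as helpers. The protection that it does state is blind analysis.

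**The concern.** In the IPB arms, a parent may be asked whether the household has a fire escape plan by a member of staff from the centre that was asked to teach escape planning over the preceding year. The socially desirable answer is obvious, and the person asking has an interest in it. Control staff may also help parents, but they were not given the IPB or asked to promote its messages, so the pull towards a yes is plausibly weaker there. Any gap between arms in this over-reporting goes straight into the estimated effect.

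The same questionnaire also informs satisfaction with the centre's home safety information and receipt of its advice and sessions (Family participants, items 7 and 8). Some parents could therefore be rating the centre in front of its own staff.

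Unblinded families are unavoidable here. Having the centre's own staff present when the answer is given is not, because the article already provides other routes.

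**Working it through.** **Step 1. Set the passages side by side.**

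| Question | What the article states | Section |
|---|---|---|
| What is measured? | Family's own report of a plan | Definition of primary and secondary outcome measures |
| Who teaches it in the IPB arms? | The children's centre | Allocation to intervention and delivery of intervention |
| Who may complete the questionnaire with the family? | Centre staff or researchers, besides post and telephone | Ascertaining family outcomes |
| Are staff blind? | No | Blinding |
| Is the staff route acknowledged in the discussion of masking? | No; only researchers are discussed as helpers | Blinding |

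**Step 2. Does any described analysis act on it?**

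- Blind analysis operates after the answers are recorded.
- The primary model adjusts for site, lead agency, two Ofsted scores, baseline plan and IMD. None of these measures over-reporting that arises after allocation.
- The sensitivity analyses under Missing data (multiple imputation; no change from baseline) concern families without an answer, not families whose answer was influenced.

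**Step 3. Reproduce the design figures used below.** Inputs from Sample size: 42% versus 62%, 80% power, two-sided 5%, ICC 0.05, 20 families per centre.

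- Uncorrected n per arm = [1.96 × √(2 × 0.52 × 0.48) + 0.8416 × √(0.42 × 0.58 + 0.62 × 0.38)]² / 0.20² = 96.8, so 97.
- With continuity correction: (96.8/4) × [1 + √(1 + 4/(96.8 × 0.20))]² = 106.5, so 107.
- Design effect = 1 + 19 × 0.05 = 1.95.
- Centres per arm = 107 × 1.95 / 20 = 10.43, so 11, as stated.

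The sample size is sound and this point does not change it.

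**Step 4. Illustrate the size.** The documents give neither the share of assisted questionnaires nor the degree of over-reporting, so both are assumptions:

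- f = share of questionnaires completed with a helper, taken as equal across arms;
- b = excess probability of a false yes among assisted families without a plan, IPB arm minus control.

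With no true effect and 42% truly having a plan, the spurious difference is f × b × (1 − 0.42) = f × b × 0.58. The effective sample per arm is 11 × 20 / 1.95 = 112.8.

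Worked case, f = 0.50 and b = 0.20:

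- Difference = 0.50 × 0.20 × 0.58 = 0.058, so the reported proportions are 0.420 and 0.478, with mean 0.449.
- SE = √(2 × 0.449 × 0.551 / 112.8) = 0.066.
- Shift = 0.058 / 0.066 = 0.88 standard errors.
- Two-sided type I error = P(Z > 1.96 − 0.88) + P(Z < −1.96 − 0.88) = 14.1%.

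| f | b | Spurious difference (points) | Two-sided type I error |
|---|---|---|---|
| 0.10 | 0.10 | 0.6 | 5.1% |
| 0.25 | 0.20 | 2.9 | 7.2% |
| 0.50 | 0.20 | 5.8 | 14.1% |
| 0.50 | 0.30 | 8.7 | 25.9% |

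This is an unadjusted two-proportion approximation. It shows an order of magnitude and does not predict what the planned model would give.

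**The case against.** The best defence is that the limitation is largely disclosed and probably small. The Blinding section says that staff, families and assisting researchers all know the arm. The questionnaire is nominally self-completed, researcher support is framed as being for parents who need it, and face-to-face completion is one option among several. This stands as a limit on size: nothing shows that assistance will be common, although the Discussion expects literacy and mobility problems and gives these as the reason for varied follow-up methods. It does not answer the narrower point, because the staff route is neither acknowledged nor necessary.

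Four stronger readings are tempting, and the documents do not support them.

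- *Bias in the intervention arms only.* Staff may assist in all three arms, and control centres continue their usual home safety information. Wanting to please familiar staff can raise reporting there too. Only the difference between arms matters, and its direction is an inference.
- *Researchers who assist are also the teachers.* The research team shares in training, and there are "facilitation contacts between children’s centres and researchers", but both are directed at centres, and the IPB-only arm is to receive neither training nor facilitation. No passage shows assisting researchers teaching families, or the same individuals in both roles.
- *The Blinding section ignores centre staff.* It names them as unblinded. It omits only their role as questionnaire helpers.
- *A known loss of 10% to 50% of the target difference.* Assuming 20% to 50% assisted in the IPB arms and 10 to 20 points of over-reporting among them gives 0.2 × 10 = 2 to 0.5 × 20 = 10 points. Both inputs are invented, and control over-reporting is set to zero.

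Two further objections stand in part. Withdrawing staff help may cost responses in a complete-case analysis that already allows for 33% loss, so some reporting bias could be exchanged for attrition bias. Recording of completion mode may sit in a fuller document that is not shown, so its absence from the article is not held against the plan.

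**Conclusion.** The point holds as a design weakness that is cheap to repair. The article permits staff of the delivering centres to complete the primary-outcome questionnaire with families, its account of masking does not acknowledge this, and no analysis it describes acts on the resulting reporting bias. A bias favouring the IPB arms is plausible but not demonstrated.

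The size cannot be derived from the documents. The range of 0.6 to 8.7 points rests wholly on assumed values of f and b. At the low end the effect is negligible; at the high end it could contribute to a false positive. The case for change therefore rests on how easily the risk is avoided, not on an estimate of harm. The stated sample size is unaffected.

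**What to change.** 1. **Staff role.** At follow-up, centre staff may hand out the questionnaire or prompt its return for sealed self-completion, but may not complete it with families.
2. **Help where needed.** Use the telephone or researcher routes already in the article, preferably an existing researcher from another of the four sites who is not told the allocation. Ask the fire escape plan item before any item on advice or sessions received, since those answers may reveal the arm.
3. **Record and report.** Note completion mode and helper for every questionnaire and report both by arm.
4. **Sensitivity analysis.** If any staff-assisted responses still occur, repeat the primary analysis without them. Treat this as a sensitivity analysis only: mode arises after randomisation and may differ by arm, so the restricted comparison is not itself protected by randomisation.
5. **Blinding section.** State who may assist at follow-up and what they know of the allocation.

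The cost is procedural wording, two recorded fields and some reassigned calls. The downsides are possibly a somewhat lower response among families who would have used staff help, and masking of callers that is only partial.

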### Ascertaining children’s centre outcomes

Information will be collected from children’s centres managers or staff on the promotion of fire prevention using a postal questionnaire at baseline and post intervention in the IPB plus facilitation arm and the IPB only arm, and at baseline and 12 months post randomisation in the control arm. Questions will be based on those used in a national survey of injury prevention activity amongst children’s centres in England [28]. Questions concerning resource use related to implementing the IPB will be included in the post-intervention questionnaire for all arms of the trial. The baseline questionnaire was piloted on 10 children’s centres across England who were not selected to take part in the trial and minor modifications were made.

During the intervention period, data on process measures such as the number of fire prevention sessions provided by the children’s centre, number of centres with a written plan for implementing the IPB, number of staff trained in delivering the IPB per centre, number of specific fire safety sessions from the IPB provided for parents and number and type of other methods used by each centre to reach parents with fire safety messages (e.g. home visits by outreach workers, incorporation of fire safety messages in existing activities) will be ascertained from the IPB plus facilitation arm through the facilitation contacts questionnaire and interviews and the activity logs.

Post-intervention, information on the implementation of the IPB will be ascertained from an implementation fidelity questionnaire and from implementation fidelity interviews, with centre managers and/or staff responsible for the delivery of the IPB in the IPB plus facilitation and the IPB only arms of the trial. The questionnaire and interview schedule will be based on the Carroll framework [21], on the review of the literature on the implementation and facilitation of health promotion interventions undertaken for the trial, the systematic review of barriers and facilitators to home injury prevention [11] and findings from interviews of children’s centre managers and staff described above. Data collected from the range of outcome measurement tools will be mapped onto the PARIHS framework [20] (described above) to explore the success of the implementation process.

### Sample size

Eleven children’s centres per arm are required to detect an absolute difference in the percentage of families with a fire escape plan of 20% in either of the two intervention arms compared with the control arm. This assumes a control arm prevalence of 42% ascertained from a structured interview completed by families attending children’s centres in the four study centres [24], an intraclass correlation coefficient of 0.05, that outcomes are assessed on 20 families per children’s centre and is for 80% power and a 5% significance level (2-sided). This gives a total of 33 children’s centres. We will recruit a total of 36 children’s centres (9 per trial site), which will also allow for potential drop-out of one children’s centre per trial arm. Allowing for 33% loss to follow-up among families, 30 families per children’s centre will be recruited, a total of 1080 families.

### Randomisation

Once 30 families have been recruited at a children’s centre, centres will be stratified by trial site (4 strata: Nottingham, Bristol, Norwich, Newcastle) and randomly allocated within strata to one of three arms using permuted block randomisation, with a block size of 3. The allocation schedule will be produced by an independent statistician, using the randomisation algorithm in Stata. These lists will be provided to an independent administrator who will prepare sequentially numbered opaque envelopes (one set for each of the four trial coordinating centres) with these allocations.

Children’s centres will be randomised in trios, once each stratum contains 3 children’s centres. In this way, allocation will be concealed from the children’s centres and the researchers up to the point of actually randomising a trio of centres. Once a stratum contains 3 children’s centres, the administrator will open the envelopes for each block of 3 children’s centres, record the allocations and notify each of the trial coordinating centres of the allocation. Children’s centres will then be notified of their allocation by email.

### Blinding

It is not possible to blind children’s centre managers and staff or those providing the intervention to treatment arm allocation. As with many public health interventions, it is not possible to blind families to receipt of the intervention and as outcomes are self-reported, data on these cannot be collected blind to treatment arm allocation. If parents require support from a researcher to complete the follow-up questionnaire the researcher will not be blind to children’s centre treatment arm. Analyses will be undertaken blind to treatment arm allocation.

### Withdrawals

Participants will be free to withdraw from the trial at any stage but their data will be included up to the date of withdrawal. However, in order to minimise losses to follow-up, every effort will be made to maintain contact with families, even if they move to an area covered by a different children’s centre.

### Analysis

Baseline characteristics will be described for the three treatment arms using frequencies and percentages for categorical variables and with means and standard deviations for continuous variables if normally distributed or, if not, with medians and interquartile ranges.

All analyses of primary and secondary outcomes will be conducted on an intention-to-treat basis in that families and children’s centres will be analysed in the group to which they were randomised, regardless of whether they received or delivered the intervention. Analyses will be undertaken blind to treatment arm allocation. Statistical significance will be assessed based on likelihood ratio tests with a p value of <0.05 taken as significant. Analyses will be undertaken using Stata.

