### Primary outcome measure

The proportion of families who report that they have a fire escape plan will be compared between treatment arms (IPB plus facilitation versus control and IPB only versus control) using random effects logistic regression to estimate odds ratios and 95% CI. The model will include randomisation stratum (trial site: Nottingham, Bristol, Norwich, Newcastle) as a fixed effect and will adjust for three cluster level variables (lead agency of the children’s centre (Local Authority, NHS or Voluntary sector led), Ofsted report scores for overall effectiveness and capacity for sustained improvement [29]) and two family level variables (having a fire escape plan at baseline and the Index of Multiple Deprivation (IMD) 2010 score [14]). These variables were selected as they are considered likely to be strongly associated with the outcome variable. The main comparisons will be between the IPB plus facilitation group versus control and the IPB only group versus control; a significance level of 0.05 will be used for each of these comparisons. Sub-group analyses will explore differential effects of the interventions by IMD, by adding interaction terms to the regression model. The intraclass correlation coefficient with a 95% CI will be estimated from the random effects regression model.

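### Uncorrected likelihood ratio tests on 33 to 36 centres, with 10 or more centre-level parameters, give each primary comparison a type I error of about 9-12% at the planning ICC, not 5%

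*Protocol article*

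**What the plan says.** The decision rule is in the protocol's Analysis section: "Statistical significance will be assessed based on likelihood ratio tests with a p value of <0.05 taken as significant". Under Primary outcome measure, the two intervention arms are each compared with control "using random effects logistic regression to estimate odds ratios and 95% CI", and "a significance level of 0.05 will be used for each of these comparisons". The same section puts site in the model as a fixed effect. It also adds lead agency (three types), two Ofsted scores, baseline fire escape plan and IMD score. Family-level secondary outcomes get random effects models with the same structure.

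The Sample size section sets the number of independent units. It asks for 11 centres per arm to "detect an absolute difference in the percentage of families with a fire escape plan of 20% in either of the two intervention arms", assuming "an intraclass correlation coefficient of 0.05, that outcomes are assessed on 20 families per children’s centre" and 42% prevalence in the control arm. "This gives a total of 33" centres; 36 are to be recruited to cover drop-out. No degrees-of-freedom or small-sample adjustment appears anywhere.

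**The concern.** Arm is a property of the centre, so the precision of each arm effect depends on the between-centre variance, and that must be estimated from 33 to 36 centres. Maximum likelihood does not allow for the centre-level coefficients already fitted, so its variance estimate is too small. A likelihood ratio test referred to chi-squared then rejects too often. REML cannot be read into the text as a remedy, because comparing models with and without a fixed arm term requires maximum likelihood.

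At stake is the trial's main conclusion. If the true level is well above 0.05, an ineffective briefing or facilitation package would be declared effective more often than the protocol claims.

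**Working it through.** **1. The plan's own figure reproduces.** Comparing 42% with 62% at two-sided 5% and 80% power needs 97 families per arm, or 107 with continuity correction. The design effect is 1 + 19 × 0.05 = 1.95. Then 107 × 1.95 / 20 = 10.43, rounded up to 11 per arm. The sample size is not at fault.

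**2. Centre-level parameters.** Intercept 1 + arm 2 + site 3 + lead agency 2 = 8. The two Ofsted scores add 2 if linear (total 10) or 4 if each has three categories (total 12). The coding is not stated. Residual centre degrees of freedom run from 33 − 12 = 21 to 36 − 10 = 26.

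**3. Mechanism.** On the logit scale an ICC of 0.05 is a centre variance of (0.05/0.95) × π²/3 = 0.173. The sampling variance of a centre's logit is about 1/(20 × 0.42 × 0.58) = 0.205, so the total is 0.378. Maximum likelihood shrinks the total by roughly (K − p)/K. With 36 centres and 10 parameters this is 0.378 × 26/36 = 0.273, leaving 0.273 − 0.205 = 0.068 for the centre variance. Simulated estimates averaged 0.05-0.07 against a true 0.17. In 18-44% of simulated trials with 10-12 parameters the estimate was near zero.

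**4. Size of the test.** If all variance lay between centres, the 1-df test against 3.84 would reject when F(1, K − p) exceeds (K − p)(exp(3.84/K) − 1). For K = 36 and p = 10 the cutoff is 26 × (exp(0.1067) − 1) = 2.93, which gives 9.9%. No covariate distribution has to be assumed for this.

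The planned model was also simulated under no effect, in separately coded runs with ICC 0.05, 20 families per centre and all listed covariates. The covariate distributions were assumed.

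| Centres / parameters | Closed form | Simulated size per comparison |
|---|---|---|
| 36 / 10 | 9.9% | 9.0-9.8% |
| 36 / 12 | 11.3% | 10.5% |
| 33 / 10 | 10.6% | 9.5% |
| 33 / 12 | 12.2% | 10.8-11.6% |

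With arm and site as the only centre-level terms (36 centres, 6 parameters) the simulated size is 7.5%.

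**5. Dependence on the ICC left after adjustment.**

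| Residual ICC | Centres / parameters | Simulated size |
|---|---|---|
| 0.10 | 36 / 12 | 11.2% |
| 0.02 | 36 / 10 | 7.8% |
| 0.01 | 36 / 10 | 5.9% |
| 0 | 36 / 10 | 4.5% |

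The last two rows rest on 900 trials each.

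**6. Alternatives at ICC 0.05.** Referring the same statistic to F(1, df) leaves the size at 7.6-9.2%, because the variance estimate is still too small. A two-stage centre-level analysis with t on K − p degrees of freedom gives 4.8-6.1%.

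**7. Power of the two-stage analysis.** For 42% against 62%, with covariates unrelated to outcome:

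| Centres / parameters | Power |
|---|---|
| 36 / 10 | 82% |
| 36 / 12 | 78% |
| 33 / 10 | 77% |
| 33 / 12 | 73% |

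Simulation at an assumed conditional log odds ratio of 0.9 gave about 83% (36 / 10) and 75% (33 / 12).

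**The case against.** The best counter-argument concerns the ICC. The 0.05 is a planning value, used in a calculation without covariates, whereas the test depends on what remains after adjustment. The protocol chose its covariates because it expects them to be strongly associated with the outcome, and site is in the model too. If they absorb most of the centre variance, the inflation is slight. This stands: a flat statement that the error rate doubles goes beyond the documents. Equally, the protocol offers no smaller residual value, and 0.05 is the only one it commits to.

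It can also be said that the text never mentions chi-squared and that an analysis plan not shown may add a correction. This carries less weight. The protocol itself fixes the test, the model and the covariates, and chi-squared is the default reference for an unqualified likelihood ratio test.

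Four stronger readings are tempting and are not supported:

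- **That every p value is affected.** The centre-level outcomes use ordinary logistic or linear regression and fall outside this point. For family-level secondary outcomes the mechanism is the same, but only the binary primary outcome was simulated.
- **That the whole chance of at least one false positive is due to the test.** That chance is 16-19% at ICC 0.05. Testing two comparisons at 0.05 each, which the protocol openly does, already allows up to about 10%.
- **That the confidence intervals are shown to under-cover.** Intervals from the same fit would share the understated variance, but coverage was not computed and the protocol does not say how the intervals are built.
- **That correcting the test is free because 11 centres per arm still give about 83% power.** That figure uses t on 20 degrees of freedom and ignores the centre covariates that the corrected analysis would include.

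**Conclusion.** The concern holds for arm comparisons on family-level outcomes, and above all for the two primary comparisons. On the protocol's own inputs the stated 5% level is about 9-12% per comparison with 10 or 12 centre-level parameters. The full range runs from near nominal (4.5-6% at a residual ICC of 0 to 0.01), through about 8% at 0.02, to 9-12% at 0.05.

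This assumes the default chi-squared reference, maximum likelihood fitting, 20 analysed families per centre and assumed lead-agency and Ofsted distributions. The closed form needs no such distributions and agrees closely. Because the rule governs the primary conclusion and the residual ICC cannot be known in advance, the plan should not depend on its being small.

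**What to change.** For arm comparisons on the primary outcome and the family-level secondary outcomes, replace the uncorrected likelihood ratio test with one of the following, named in advance:

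- **Two-stage centre-level analysis.** Fit the family covariates (baseline value and IMD) without arm. Average the residuals by centre, then regress them on arm, site, lead agency and the Ofsted scores. Use t on centres minus centre-level parameters.
- **Permutation test.** Re-randomise arm labels within the randomised trios, with the planned model's statistic as the test statistic. Its validity comes from the randomisation; it was not simulated here.

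Take the 95% CI from the same procedure as the p value. The two-stage interval is on the scale of a difference in proportions, which is also the scale of the sample size target. Keep the random effects odds ratio as a descriptive estimate. State the coding of the Ofsted scores, since it sets the degrees of freedom. Changing only the reference to F, or dropping the centre covariates but keeping the test, would not be enough at ICC 0.05 (7.6-9.2% and 7.5%).

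The cost is analysis wording, a little programming and some power. With 36 centres and 10 parameters power is about 82-83%. With 33 centres or 12 parameters it is about 73-78% if the covariates explain no centre variance, and higher if they do. Recruitment and data collection do not change.
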